### Outcomes

#### Co-primary feasibility outcomes

Uptake rate as a percentage of the number of eligible participants invited who consent to take part for the trial.Retention rate measured as the number of consented participants who complete the 16-week trial.Self-reported adherence to the 6:1 programme across the 16-week trial.Patient acceptability of the 6:1 programme using a validated intervention evaluation questionnaire at the end of the programme or at time of withdrawal from the trial.^28^

#### Other outcomes include

Key characteristics of those recruited versus the overall population in this age group in the main recruiting regional FHC.Key characteristics of those recruited who withdraw versus those who complete the trial.Fidelity of delivery and participant engagement with the programme: dietitian time required for delivery of the programme and participation engagement with the dietitian calls and the private 6:1 trial Facebook group. There are no plans to collate qualitative comments from the Facebook group.Preliminary evaluation of any benefits:Changes in body weight and body composition; body fat and fat free mass (assessed with bioelectrical impedance), waist and hip circumferences.Changes in diet quality using the Mediterranean diet score.^29^Changes in alcohol intake and smoking using 7-day recall.^30^Changes in physical activity using the International Physical Activity Questionnaire (IPAQ) short form.^31^Change in objectively measured physical activity assessed with an ACTigraph.Preliminary evaluation of any possible harms:Changes in eating behaviours using the BES.^22^Change in sleep quality assessed using the PSQI.^32^Potentially diet related adverse events including fatigue, constipation, dizziness, headache, indigestion in the 4 weeks before starting the diet and four weekly throughout the programme at each dietitian review call as defined by Common Terminology Criteria for Adverse Events (CTCAE) V.5.^33^Change in mean menstrual cycle length during the trial from self-reported diaries.

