The trial will also assess if the diet could be associated with any harms. We will assess the effects of the diet on disordered eating. Intermittent weight loss diets have mainly demonstrated improvements in eating patterns in the weight loss setting,^10 11^ but some concerns have been expressed of increased eating related thoughts, hunger and fear of loss of control among healthy-weight individuals consuming such diets.^12 13^ There is also evidence that reduced calorie intakes may be associated with reduced physical activity and reduced energy expenditure, in order to conserve energy, with potential detrimental effects on lean body mass.^14^ Some people following energy restricted diets report poorer sleep quality,^15^ although findings are not consistent.^16^ The planned trial therefore includes assessments of dietary intake, an objective measure of physical activity (ACTi graph),^17^ sleep quality (Pittsburgh Sleep Quality Index (PSQI)) and body composition (bioelectrical impedance, Tanita MC980MA), waist, hip circumferences to obtain preliminary data of these effects.

As there is a potentially bi-directional relationship between low-calorie diets and menstrual cycle in young women, we will ask participants to record the first day of their menstrual cycle throughout the trial. This is being done for completeness as we do not anticipate the modest energy restriction with the 6:1 intermittent diet will directly affect menstrual cycle function which can occur with longer spells of low-calorie intake.^18^ Inclusion of menstrual cycle dates will also provide preliminary data of any potential differences in dietary adherence across the menstrual cycle and whether adherence is reduced in the premenstrual weeks when women often report increased appetite and carbohydrate craving.^19^

In line with guidance on best practice in evaluating complex interventions, it is important to test the acceptability and any potential benefits and harms of this novel diet in a feasibility trial, as well as assess the major uncertainties in conducting an efficacy trial of this diet.^20^ The evaluation of acceptability, adherence and exploratory evaluation of weight and health behaviours and patient experience in the trial will determine whether we should proceed to a larger efficacy trial.

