### Measurements

The full schedule of assessments is described in table 2.

**Table 2 T2:** Schedule of assessments for participants in the Prevent 6:1 Trial

Procedures	Screening/baseline	Week 0	Week 4 (±7 days)	Week 8 (±7 days)	Week 12 (±7 days)	Week 16 (±7 days)
Informed consent	x					
Screening questionnaires GAD (anxiety), PHQ (depression), AUDIT (alcohol dependence)	x					
BES (Binge Eating Scale)	x			x		X
Pregnancy test where required*	x					
Medical history	x					
PAR-Q readiness to exercise questionnaire	x					
Demographic/dieting history questionnaire	x			Update any changes		Update any changes
Assessment of menstrual cycle dates across the trial			x	x	x	x
Adherence to the low-calorie day each week across the trial			x	x	x	x
Body weight, body fat and lean body mass (bioelectrical impedance), waist/hip circumference	x					x
Mediterranean diet questionnaire	x			x		x
7-day food diary on Myfood 24 or paper diary	Completed week after baseline visit			x		Complete in week before week 16 visit
Alcohol intake (7-day recall), smoking and vaping questionnaire	x			x		x
Wear ACTigraph physical activity monitor for 7 days	Complete in week after baseline visit					Complete in week before week 16 visit
IPAQ short form (physical activity)	x			x		x
PSQI (sleep quality)	x			x		x
Intervention evaluation questionnaire and self-reported acceptability data						x
Baseline and exit face-to-face diet and physical activity advice		x				x
Dietitian review phone or video call/email			Offered dietetic support via phone or video call (MS teams) or email reviews at weeks 1, 4, 8, 12			
Assessment of dietitian time spent delivering the intervention			x	x	x	x
Assessment of engagement with dietitian calls/emails/online sessions and private Facebook group			x	x	x	x
Recording potentially diet related adverse events in the previous 4 weeks	x		x	x	x	x
Home weight recording and reporting to dietitian			x	x	x	
Optional anonymous NIHR demographic questionnaire	x					

* Pregnancy test is not required if the participant meets NICE criteria for excluding pregnancy (negative predictive value of 99%–100%) (https://cks.nice.org.UnitedKingdom/topics/contraception-assessment/management/assessment-for-contraception/): Is within the first 5 days of the onset of a normal (natural) menstrual period. Has not had sexual intercourse since the start of last normal menses. Has been correctly and consistently using a reliable method of contraception.

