### Questionnaires

Participants will be asked to complete four paper questionnaires at the baseline visit to check eligibility; GAD-7,^23^ PHQ-9,^24^ BES,^22^ AUDIT.^38^ Eligible recruited participants will be asked to complete further questionnaires at baseline, weeks 8 and 16 (alcohol intake and smoking using 7-day recall,^30^ PSQI^32^ Mediterranean diet score,^29^ IPAQ^31^ using a secure web application (REDCap) (figure 1).^39^ A trial demographic questionnaire will also be requested at baseline. They will also be asked to complete an optional anonymous National Institute of Health Research (NIHR) demographic questionnaire. The NIHR is funding this project and they would like to understand whether research is reaching under-represented groups to help shape future research. Participants are informed their responses to questions are anonymous (not linked to their name or another identifier) and may be used for other educational and research purposes in the future.

Participants will also be asked to complete a trial specific diary over the 16-week programme, which records adherence to the low-calorie day of the 6:1 diet for each week and first day of each menstrual cycle while on the trial.

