### Adverse events

Potentially diet related adverse events, that is, constipation, diarrhoea, dizziness, fatigue, headache, indigestion will be recorded retrospectively for the 4 weeks prior to baseline and prospectively every 4 weeks throughout the trial during the dietitian reviews using CTCAE V.5.0. Any grade 3 or grade 4 adverse events will be discussed with the trial management group. We will report any serious adverse events (SAEs) to the sponsor within 24 hours of the chief investigator becoming aware of the event. SAEs that are related and unexpected will be reported to the research ethics committee within 15 days of the chief investigator becoming aware of the event.

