### Implications and future directions

Success of this feasibility trial will be defined by the progression criteria described in table 3. If these criteria are met, funding will be sought for a future efficacy trial.

**Table 3 T3:** Progression criteria to an efficacy trial of the 6:1 diet intervention

Progression criteria	Feasible (green)	Feasible with modification of the protocol (amber)	Not feasible (red)
Recruitment	≥6 patients/month	3–5 patients/month	≤2 patients/month
Uptake to the feasibility trial	>15%	10%–15%	<10%
Retention to the feasibility trial	>70%	50%–70%	<50%
Adherence to the ILED diet: % of the low-calorie days completed (1 day/week for 16 weeks)	>50%	30%–50%	<30%
Safety concerns: evidence of increased binge eating/reduced sleep/reduced physical activity/reduced diet quality	Reported in <10% of participants	Reported in 10%–20% of participants	Reported in >20% of participants

ILED, Intermittent Low Energy Diet.

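### The menstrual harm outcome is a mean of cycle lengths taken from first-day dates, so it cannot register periods that stop; add a per-woman longest-gap count from the same diary

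*Protocol article*

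**What the plan says.** Under Other outcomes, among the possible harms, the protocol article lists "Change in mean menstrual cycle length during the trial from self-reported diaries".

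The data come from a trial diary, which the Questionnaires section says "records adherence to the low-calorie day of the 6:1 diet for each week and first day of each menstrual cycle while on the trial". The Introduction gives the same instruction: "we will ask participants to record the first day of their menstrual cycle throughout the trial". In the schedule of assessments (Table 2), the row "Assessment of menstrual cycle dates across the trial" is marked at weeks 4, 8, 12 and 16, with no mark apparent at screening/baseline or week 0.

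The Introduction presents the dates as collected for completeness: "we do not anticipate the modest energy restriction with the 6:1 intermittent diet will directly affect menstrual cycle function". It links effects on cycle function to longer periods of low-calorie intake.

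Two other places could pick up a menstrual harm, and neither does. The solicited events in the Adverse events section are "constipation, diarrhoea, dizziness, fatigue, headache, indigestion will be recorded retrospectively". The safety row of the progression criteria (Table 3) covers "evidence of increased binge eating/reduced sleep/reduced physical activity/reduced diet quality".

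The Data analysis plan is descriptive and says that the level of missing data will be reported. The article does not say how an unfinished last cycle, or a woman with fewer than two recorded first days, is handled.

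**The concern.** A mean cycle length can be computed only from cycles that have closed. If a woman stops menstruating, the interval that carries the information is the one that never closes, and it has no length to average. The measure therefore responds to cycles that lengthen and then resume within 16 weeks, but not to cycles that cease.

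At stake is what a reader could conclude from the report. An unchanged mean cycle length would be taken as reassurance about menstrual function, although the same figure would appear if some women had stopped menstruating. No other listed outcome, solicited event or progression criterion would report them.

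**Working it through.** **Inputs from the article.** Diary length 16 weeks = 112 days; data = first-day dates only; planned sample 30 women. **Assumptions, not in the article:** a usual cycle of 28 days (range 26 to 35) for the enumeration; for the simulation, a mean of 29 days, between-woman SD 2.5, within-woman SD 2.5 and a random starting phase. The article states no figure for this outcome, so there is none to reproduce.

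**Step 1: three diaries.** Cycle length = difference between successive first days; open interval = 112 − last first day.

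| First days | Completed cycles | Mean | Open interval |
|---|---|---|---|
| 5, 33, 61, 89 | 28, 28, 28 | 28 | 112 − 89 = 23 |
| 5, 33, then none | 28 | 28 | 112 − 33 = 79 |
| 5, then none | none | no value | 112 − 5 = 107 |

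The first two women have the same mean; the third has none.

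**Step 2: enumeration over every possible first day, 28-day cycle.** No first day occurs after the stated day.

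| Last possible first day | Women with no completed cycle | Completed cycles among the rest | Open interval (days) |
|---|---|---|---|
| 28 | 100% (92–100% for 26–35-day cycles) | none | 84 to 111 |
| 42 | 50% (38–80%) | one, of normal length | 70 to 97 |
| 56 | 0% (0–40%) | one, of normal length | 56 to 83 |
| 84 | 0% (0%) | two, of normal length | 28 to 55 |

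In no row does the open interval enter the mean. A change computed within the trial needs at least two completed cycles. With 28-day cycles, no woman who stops by day 56 has two, so her change is missing, not zero.

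**Step 3: effect on the group mean.** Take first days on days 14 and 42, then none. Completed cycles give 28, a change of 0 against a usual 28. Counting the open interval of at least 112 − 42 = 70 days gives (28 + 70)/2 = 49, a change of at least +21. With k such women among 30 and no change in the others, the group change is at least 21k/30:

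- k = 1: 0.7 days
- k = 3: 2.1 days
- k = 6: 4.2 days

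On completed cycles it is 0 in all three cases.

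**Step 4: simulation, 40,000 women per scenario.** In the cessation scenarios, 20% of women have no further menses after their first period on or after the stated day. The last column counts an interval, open or closed, of more than 45 days.

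| Scenario | Mean of completed cycles | Affected women with no value | All women flagged (>45 days) |
|---|---|---|---|
| No effect | 29.0 | – | about 0% |
| Cessation, day 14 | 29.0 | 51% | about 20% |
| Cessation, day 28 | 29.0 | 6% | about 20% |
| Cessation, day 56 | 29.0 | 0% | about 8% |

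In the day-28 scenario, 90% of affected women have a mean below 35 days. The flag falls to 8% for day 56 because the last period then falls roughly between days 56 and 84, leaving an open interval of about 28 to 56 days; many of these have not yet passed 45 days.

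**Step 5: would a Kaplan–Meier summary repair it?** With all cycles pooled and open intervals censored, the median is 28.8 days with no effect and 29.1 days in the day-28 scenario. The estimated proportion beyond 45 days is about 8% in that scenario, against 20% of women affected, because it counts cycles, not women.

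**The case against.** The strongest objection is that the article states no rule that discards the open interval. It gives one outcome line, and deriving a secondary variable is ordinary analysis-plan content. That stands as far as it goes: the treatment of an unfinished cycle may be set out in a document not shown. But the article does fix the summary as a mean of cycle lengths and the data as first-day dates. On the ordinary reading only completed cycles count, and a separate plan could register cessation only by adding something to this outcome.

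A reader might go further and infer that a woman who stops menstruating is scored as unchanged. The documents do not support that as a rule. Early cessation gives a missing value, and the article promises to report missing data. A zero change needs either two completed cycles or a usual length to compare with, and no pre-diet cycle date appears in the schedule. What remains is narrower: late cessation produces no missing mean, a blank diary looks the same as absent menses, and in every case the group mean is essentially unaffected.

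A reader might also infer that the trial would fail to notice cessation at all. That is not supported either. Dates are reviewed four times in about 30 women, so a long gap would be visible in the data; it is the listed summary that leaves it out.

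Nor does the article say that this diet is expected to disturb menses. It says the opposite, and ties such effects to longer low-calorie periods. The 20% rate has no basis in the article. The near-zero flag rate with no effect assumes complete diaries and regular cycles. Eligibility allows contraception and does not exclude hormonal methods, so some long gaps will have nothing to do with the diet.

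**Conclusion.** The point holds as a limitation of the summary measure. As defined, change in mean cycle length cannot register cessation of periods: affected women contribute earlier normal cycles or no value. The group mean stays at 29.0 days in every cessation scenario tried, and no listed adverse event or progression criterion covers absent periods. That the open interval is left out follows from the data fixed in the article. The sizes rest on the assumed cycle distribution and an illustrative 20% cessation rate.

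The practical weight is modest. This is a non-primary outcome in an unpowered feasibility trial, no progression decision depends on it, and the sponsor expects no direct effect. It is still worth correcting, because the outcome is presented as a harm check and a count from the same diary would show what the mean cannot.

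**What to change.** Keep the mean, and add to the outcome, from the same diary:

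- each woman's longest interval between first days, including the open one from her last recorded first day to week 16 or her last diary date;
- the number and percentage of women whose longest interval exceeds a length set in advance (45 days is used above only as an illustration);
- the number of women with fewer than two recorded first days.

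When cycle dates are reviewed, record a confirmation that there has been no period since the last date given, so that a blank diary is not read as absent menses. Report women using contraception that suppresses bleeding separately.

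A pooled Kaplan–Meier summary is not recommended as the main repair, since its median is nearly as insensitive as the mean.

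The cost is one extra descriptive line and one question at reviews that already take place. Two limits remain: gaps can still arise from contraception or incomplete diaries, and cessation late in the 16 weeks will be only partly flagged.

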### Trial setting and recruitment

Participants will be identified from the regional FHC and the Cancer Genetics Clinics at Manchester University NHS Foundation Trust (MFT). Recruitment will be through direct invitation by members of the clinical teams, mailing the patient information sheet and promotion via the Prevent Breast Cancer charity website and related social media platforms such as Facebook and X. These women will have their attendance at the FHC and genetics clinics verified by a member of the relevant teams. The planned trial start and end dates are 17 March 2025 and 17 March 2026. All trial face-to-face assessments will be undertaken by the research team in a research facility at the main recruiting site at Wythenshawe Hospital. All participants will have a trial run-in week before they receive baseline diet advice when we ask them to record 7 days of habitual diet and wear an activity monitor to assess their habitual diet and physical activity patterns.

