Box 1Inclusion and exclusion criteria for the Prevent 6:1 trialInclusion criteriaAged 18–40 years.Born female and not undergone gender reassignment X.Moderate or high risk of breast cancer (≥17% lifetime risk or with 10-year risk of breast cancer of ≥3% at 40)^21^ and have attended/currently attending NHS family history/genetics clinic.BMI 20–25 kg/m^2^.Able to communicate (written and spoken) in English or any other language and access to a phone as we have access to an interpreter service.Able to attend two face-to-face appointments at MFT at baseline and week 16.Not pregnant or planning to become pregnant in the next 16 weeks. Where appropriate, participants will need to have negative urine pregnancy test at screening and agreement to maintain contraception or abstinence during the trial.Exclusion criteriaPrevious breast cancer or bilateral preventative mastectomy.Currently trying to gain weight.Previously had weight loss surgery or taking weight loss medication.Have a medical condition that influences diet and weight, for example, diabetes, inflammatory bowel disease or cystic fibrosis.Current diagnosis of a psychiatric disorder, that is, bipolar psychotic disorder or current self-harm.Current or previous diagnosis of an eating disorder.Substance abuse or harmful alcohol use as indicated by a score of 16 or above on the AUDIT Test.Severe binge eating assessed by a score of 27 or more on the BES.Severe depression assessed by a score of 15 or more on the PHQ-9.Severe anxiety assessed by a score of 15 or more on the GAD-7 questionnaire.Confirmed pregnancy via a pregnancy test, planning pregnancy in the next 16 weeks, or currently breastfeeding.AUDIT, Alcohol Use Disorders Identification Test; BES, Binge Eating Scale30; BMI, body mass index; GAD-7=General Anxiety Disorder-7; MFT, Manchester University Foundation Trust; PHQ-9, Patient Health Questionnaire-9. NHS, National Heath Service.

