#### Dietetic support

Participants will receive their initial advice to follow the diet and engage in physical activity by phone or video call after completion of the 7 days of habitual diet records and ACTigraph physical activity monitoring (week 0). They will be offered dietetic support via phone or video call (MS teams) or email reviews with one of the trial dietitians at week 1, 4, 8, 12 after starting the programme and receive exit diet and physical activity advice after their 16-week review. Trial dietitians will have previous experience and/or recent training in breast cancer risk estimation, risk factors and advising intermittent diets.

Participants will also be provided with access to a trial specific private monitored Facebook group. This includes dietitian-led online group question and answer sessions, an opportunity to raise questions and have peer support chat with other women. Also updates on information on diet, the trial and risk factors for breast cancer risk. Access to the private Facebook group is by invite only to trial participants who are reminded not to post personal information. Participants who opt to use it will be advised of the data protection policy. At the end of the trial, all participants will be removed from the private Facebook group and the site will no longer be monitored.

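### Change in menstrual cycle length is listed as a possible harm, but cycle dates are scheduled only on the diet, so change from the pre-diet state cannot be measured

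*Protocol article*

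**What the plan says.** Under Other outcomes, the list of possible harms ends with "Change in mean menstrual cycle length during the trial from self-reported diaries". The abstract places menstrual cycle length among the secondary outcomes.

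The article describes the data collection in three places:

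- **Questionnaires:** "Participants will also be asked to complete a trial specific diary over the 16-week programme". Among its entries is the "first day of each menstrual cycle while on the trial".
- **Table 2:** the row "Assessment of menstrual cycle dates across the trial" is marked at weeks 4, 8, 12 and 16. The screening/baseline and week 0 columns are empty.
- **Introduction:** "we will ask participants to record the first day of their menstrual cycle throughout the trial". Nothing is said about earlier cycles or usual cycle length.

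On timing, Trial setting and recruitment states: "All participants will have a trial run-in week before they receive baseline diet advice". Dietetic support places the first diet advice at week 0, once the 7 days of habitual records are complete. Trial design describes a single arm.

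**The concern.** In a single-arm trial, a change outcome needs a value from before the intervention, because no other group can supply the reference. The other items in the harms list have one. The binge eating and sleep questionnaires are completed at screening/baseline, and diet-related adverse events are asked about for the 4 weeks before the diet starts. Cycle length is the only item in that list with no stated pre-diet value.

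What is at stake is how the result would be read. The trial could report that cycle length did not change, and a reader planning the efficacy trial could take this as reassurance, although the scheduled data could not have shown a change that began with the diet.

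**Working it through.** The plan gives no figure for this outcome, so there is none to reproduce. The check counts how many complete cycles each recording window can hold.

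**Inputs**

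- On-diet diary window: 16 weeks × 7 = 112 days (Questionnaires).
- Pre-diet run-in: 7 days (Trial setting and recruitment; Dietetic support).
- Cycle length L: not in the document. Assumed 28 days, with a range of 21 to 35.
- The first onset falls o days into the window, with o spread evenly over 0 to L − 1.

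**Formula**

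Onsets in a window of W days = floor((W − 1 − o)/L) + 1, or 0 if o > W − 1. Complete cycles run from onset to onset, so complete cycles = onsets − 1, with a minimum of 0.

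**Worked case, W = 112 and L = 28**

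- o = 0: floor(111/28) + 1 = 4 onsets, 3 complete cycles.
- o = 27: floor(84/28) + 1 = 4 onsets, 3 complete cycles.

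**Results**

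| Window | L = 21 | L = 28 | L = 35 |
|---|---|---|---|
| Run-in, 7 days | 0 | 0 | 0 |
| Diary, 112 days | 4 to 5 (mean 4.33) | 3 | 2 to 3 (mean 2.2) |
| Both, 119 days | 4 to 5 (mean 4.67) | 3 to 4 (mean 3.25) | 2 to 3 (mean 2.4) |

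Starting the diary in the run-in week adds a little observation time but still no complete pre-diet cycle. At most, one recorded cycle would straddle the start of the diet.

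**What the scheduled data can show**

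Let a woman's mean cycle length be m before the diet and m + d in every cycle on it.

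- Late minus early on-diet cycles: (m + d) − (m + d) = 0, whatever the size of d.
- On-diet minus pre-diet: (m + d) − m = d. This needs m, which no scheduled assessment provides.

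**The case against.** Four points can be made in the plan's defence.

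1. **The wording says change during the trial, not change from before the diet.** Early and late on-diet cycles can be compared, with about 2 to 5 complete cycles per woman. This is true, but both sides of that comparison are on diet, so it misses a shift that starts with the diet and stays. The Introduction raises the question because low-calorie diets may affect the cycle, and that question needs a pre-diet reference.

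2. **Baseline forms that are not shown may hold the information.** Table 2 includes a medical history, a demographic and dieting history questionnaire, and a pregnancy-exclusion check that refers to the last normal period. This lowers certainty about what is collected in practice. It does not close the gap, because the outcome names the diaries as its source. A single last-period date joined to the first diary onset would give at most one interval, and that interval would cross the start of the diet.

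3. **The outcome carries little weight.** The Introduction says the dates are gathered for completeness and that no direct effect on the cycle is expected. The dates also serve the exploratory question of adherence across the cycle, which needs on-diet dates only. The safety row of Table 3 names binge eating, sleep, physical activity and diet quality, but not cycle length. All of this stands and limits the importance of the point.

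4. **Contraception.** Box 1 requires, where appropriate, "agreement to maintain contraception or abstinence during the trial". A reader might infer that cycles fixed by hormonal methods will be pooled with natural ones and will hide an effect. The document does not support this. It does not say that the contraception is hormonal, gives no figure for its use, and does not say how cycle lengths will be combined. That choice may properly be left to an analysis plan.

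**Conclusion.** The point holds as a minor one. On the schedule as written, the plan yields a mean on-diet cycle length from about 3 complete cycles per woman (2 to 5 over the assumed range of 21 to 35 days) and no complete pre-diet cycle. Change from the pre-diet state cannot be obtained from the stated source. The finding of no pre-diet cycle does not depend on which length in that range is assumed, since 7 days is shorter than any of them. It does rest on the article's statement that the diaries are the source.

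A reader might go further and conclude that the trial's safety assessment, or its decision to progress, is compromised. The document does not support that: the outcome is secondary, no effect is anticipated, the analysis is descriptive, and cycle length is outside the progression criteria. The risk is confined to a result of no change being read as evidence about the diet.

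**What to change.** Add a screening/baseline entry to the menstrual row of Table 2 that records:

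- the start dates of the last two or three periods, or usual cycle length if dates cannot be recalled (two dates give one complete pre-diet cycle, three give two);
- current use of hormonal contraception.

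Define the outcome as each woman's on-diet mean minus her pre-diet mean, and report it separately for women not using hormonal contraception. For women already enrolled, usual pre-diet cycle length can be asked at the next contact.

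If none of this is feasible, relabel the outcome as a description of cycle length on the diet and remove the word change.

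The cost is two baseline questions and a line in the schedule. The drawbacks are that pre-diet dates are recalled while on-diet dates are kept in a diary, so the two sides differ in accuracy, and that the subgroup will be smaller than the 30 women recruited.
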